**10.2. Severity Grading of Adverse Events**

The severity of AEs should be graded using the Common Terminology Criteria for Adverse Events (CTCAE) Version 5.0 by the U.S. National Cancer Institute (NCI).

**10.3. Assessment of Relationship Between AE and Investigational Product**

1. Investigators should evaluate the potential association between the AE and the investigational product based on the following criteria:
   1. Time of onset and time to resolution.
   2. Grading per NCI-CTCAE v5.0 definitions.
   3. Causality categorized as: definitely related, probably related, possibly unrelated, unrelated, or indeterminate. The first three categories (definitely, probably, and indeterminate) are considered related to the investigational product and will be used for calculating incidence rates of adverse reactions, with the number of such events as numerator and the total number of participants as denominator for safety evaluation.
2. All AEs or other symptoms and signs occurring during the study must be recorded on the AE page of the CRF, regardless of their relationship to the investigational treatment.
3. Any participant who receives treatment must be evaluated for toxic reactions. The severity of any AEs should be graded according to NCI-CTCAE v5.0.

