# 4. Study Design

**4.1. Overview of Study Design**

This is a phase I clinical trial, designed as a single-center, randomized (1:1), single-blind, placebo-controlled clinical study.

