5.5.2. Blinding

One research coordinator will be designated to maintain and distribute randomization numbers, prepare investigational drugs, and coordinate information among the study staff.

One study physician will be designated for patient management and data recording.
One study nurse will be responsible for administering the investigational product and monitoring safety.

Trained physicians will follow up with patients and perform additional diagnostics.

All members of the research team will remain blinded to each other’s assessments throughout the study.

5.5.3. Investigational Exosome Preparation (Derived from Human Umbilical Cord Mesenchymal Stem Cells)

Exosome nebulization solution: 2 ml/vial, containing 2×10⁹ particles.

The investigational exosome product is provided by Shanghai GenWay Cell & Tissue Storage Co., Ltd. It is derived from mesenchymal stem cells (MSCs) cultured and purified from donated neonatal umbilical cord tissue (see Section 5-0 for donor screening criteria and informed consent form, and Section 5-1 for perinatal tissue handover information). The MSC supernatant is further purified to obtain exosomes.

Informed consent is obtained from all healthy donors. Any remaining investigational products will be uniformly retrieved and destroyed after study completion.

A dedicated management system is established for the storage and distribution of investigational products. Products are delivered directly to designated personnel in the clinical research department by staff from Shanghai GenWay Cell & Tissue Storage Co., Ltd., with proper documentation for product handover.

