**7.2. Dosage and Administration**

Based on results from animal studies, prior volunteer applications, and relevant literature, the administration method is as follows:

Investigational Product

- Name: Human umbilical cord mesenchymal stem cell-derived extracellular vesicle nebulized solution
- Specification: 2 ml: 2×10⁹ particles
- Storage condition: 2°C–8°C
- Dosage and administration: Inhalation twice daily, 2 ml each time, diluted with 6 ml of normal saline and administered via nebulization at 09:00 ± 30 min in the morning and 20:00 ± 30 min in the evening, for a 7-day treatment course.

Placebo Control

- Name: Normal saline
- Specification: 8 ml
- Storage condition: Store below 25°C, avoid direct sunlight, high temperature, or freezing
- Dosage and administration: Inhalation twice daily, 8 ml each time via nebulization at 09:00 ± 30 min in the morning and 20:00 ± 30 min in the evening, for a 7-day treatment course.

To ensure patient safety, the first 4 subjects will be enrolled sequentially. Each subject will be observed for 24 hours after the initial treatment. If no adverse reactions are noted, the next subject will begin treatment. After all 4 subjects have completed the treatment, a safety assessment will be conducted before full clinical trial rollout.

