**10.6. AE Management and Follow-up**

All equipment, reagents, and techniques used in the preparation of the aerosolized EV solution follow national preparation standards and undergo strict quality control before patient administration.

Adverse reactions to aerosolized EV treatment are rare. A small number of patients may experience mild symptoms such as flushing, rash, low-grade fever, chills, nausea, or vomiting, requiring symptomatic treatment. In rare cases, patients may develop serious symptoms such as dyspnea, hypotension, tachycardia, or severe allergic reactions, necessitating immediate medical intervention.

Potential AEs and Management:：

1. Gastrointestinal reactions: 1) Use 5-HT3 receptor antagonists, corticosteroids, NK1 receptor antagonists to prevent/treat vomiting. 2) Use antidiarrheals, mucosal protectants, and intestinal antibiotics to control symptoms, promote healing, and prevent secondary infection.
2. Cardiotoxicity: 1) Avoid fluid overload; 2) Administer diuretics if needed; 3) Closely monitor ECG before, during, and 24 hours after treatment.
3. Lack of efficacy: If nebulized EVs do not alleviate symptoms or improve lung tissue repair, this has been clearly explained in the informed consent form.
4. Fever: Administer antipyretics such as acetaminophen. If persistent, investigate bacterial infection and treat accordingly.
5. Infection prevention: All EV preparation and nebulization must follow strict protocols to reduce infection risk.
6. Pain or discomfort during nebulization: Provide symptomatic relief as needed.
7. Dyspnea or mild pneumonia post-nebulization: Though rare, active treatment under close observation will be provided.
8. Cerebral embolism: Extremely rare but should remain on the alert.

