**11.5. Safety Analysis**

A detailed listing of all adverse events occurring during the trial will be provided. Changes in laboratory results (normal/abnormal) before and after the trial and their relationship to the study drug will be assessed. The incidence of adverse events in each group will be summarized. Safety analyses will be based on the Safety Analysis Set and conducted by treatment group. Treatment-emergent adverse events (TEAEs) and serious adverse events (SAEs) will be summarized. Descriptive statistics will be used to summarize laboratory findings, symptoms, vital signs, physical examinations, and ultrasound results. Abnormal values will be flagged.

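### Section 10.3 ties the adverse-reaction rate to a term that can mean the EV solution alone, so the same nebulization reaction can count under EV and be coded unrelated under saline

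*Protocol*

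**What the plan says.** Protocol 10.3, item 1, sets the causality question: "Investigators should evaluate the potential association between the AE and the investigational product based on the following criteria". It then fixes which answers feed the adverse-reaction rate: "The first three categories (definitely, probably, and indeterminate) are considered related to the investigational product". It offers no category for a relation to placebo, to the treatment as allocated, or to the act of nebulizing.

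Protocol 7.2 has two separate headings. Under the investigational product it gives "Name: Human umbilical cord mesenchymal stem cell-derived extracellular vesicle nebulized solution"; under the placebo control it gives "Name: Normal saline". Both are nebulized twice daily for 7 days, at the same volume (2 ml of EV solution plus 6 ml of saline, against 8 ml of saline).

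On blinding, 4.1 describes the trial as "designed as a single-center, randomized (1:1), single-blind, placebo-controlled clinical study", and 5.5.2 adds "All members of the research team will remain blinded to each other’s assessments throughout the study". Section 10.6 foresees events that belong to the delivery route, for example "Pain or discomfort during nebulization: Provide symptomatic relief as needed". Section 11.5 states: "Safety analyses will be based on the Safety Analysis Set and conducted by treatment group".

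**The concern.** A placebo arm that inhales the same volume on the same schedule is there to show what nebulization does on its own. That works for related events only if relatedness is judged by the same question in both arms. If the question is whether the event is due to the EV solution, and the assessor knows that the patient inhaled saline, the literal answer is no. The same cough or discomfort in an EV patient can be coded definite, probable or indeterminate, and all three count.

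What is at stake is one reported quantity: the adverse-reaction rate that 10.3 calculates for safety evaluation. It would charge reactions to the procedure to the vesicles in one arm and could drop them in the other.

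**Working it through.** The protocol gives no adverse-reaction rate, so there is no figure to reproduce. The check has two parts: a reading of the text, and a bound on the size.

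**What the term covers**

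- *EV only:* the two headings in 7.2; 10.1, which twice names the investigational extracellular vesicles when it lists what to collect; and the Safety Analysis Set in 11.1, which is limited to subjects dosed with EVs.
- *Both arms:* 5.4, which excludes anyone who never received the investigational drug (read as EV only, that would exclude every placebo subject); 5.5.1, where investigational drugs are given in order of random number; and 5.5.2, where one coordinator prepares the drugs and one nurse gives the product, with no separate role for saline.

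The document supports both readings, and 10.3 does not choose between them. It therefore permits coding that differs by arm, without requiring it.

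**Whether the assessor knows the arm**

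- *Pointing to yes:* the single-blind label; masking of staff only to each other's assessments; the sign-off in 7.1, where investigators confirm the EV product by subject name, admission number and batch; and the different specification and storage of saline in 7.2.
- *Pointing to no:* the sealed codes in 5.5.1, and the single coordinator in 5.5.2 who holds the numbers and prepares the drugs.

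On balance, knowledge of the arm is probable, but it is an inference.

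**Size**

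Inputs:

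- n = 12 per arm (section 6).
- q = rate of nebulization reactions, truly equal in both arms. This is an assumption; the documents give none.
- f = share of saline reactions coded unrelated. This is also an assumption. All such reactions under EV are taken as counted.

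Formulas:

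- Expected count, EV: 12q
- Expected count, saline: 12q(1 − f)
- Expected reported risk difference: q − q(1 − f) = fq, where the truth is 0
- Chance of at least one such reaction under EV: 1 − (1 − q)^12

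| q (assumed) | EV, expected of 12 | Saline, f = 1 | Saline, f = 0 | Reported difference, f = 1 | At least one under EV |
|---|---|---|---|---|---|
| 10% | 12 × 0.10 = 1.2 | 0 | 1.2 | 10 points | 1 − 0.9^12 = 72% |
| 20% | 12 × 0.20 = 2.4 | 0 | 2.4 | 20 points | 1 − 0.8^12 = 93% |
| 30% | 12 × 0.30 = 3.6 | 0 | 3.6 | 30 points | 1 − 0.7^12 = 99% |

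f = 1 is the worst case, and f = 0 is identical coding with no bias. If half the saline reactions were lost (f = 0.5), the difference would be 5, 10 or 15 points.

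The numerator in 10.3 counts events rather than subjects. If q is read as the mean number of reactions per participant, the result fq is unchanged; only the last column needs q to be a per-subject probability.

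**The case against.** The best defence is that this is loose terminology with little effect. Sections 5.4, 5.5.1 and 5.5.2 use the term for both arms. The denominator in 10.3 is all participants, and its item 3 calls for toxicity evaluation of anyone treated. All AEs are recorded whatever their cause, and 11.5 summarizes AEs, TEAEs and SAEs by group. Section 10.6 also calls adverse reactions to EV treatment rare, which argues for the lower end of the assumed range. All of this stands and limits the point, but none of it makes 10.3 ask the same question in both arms.

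A reader might infer three stronger things that the documents do not support:

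- *That 10.3 obliges investigators to code saline events as unrelated.* The mixed usage leaves an inclusive reading open, and unblinded assessment is nowhere stated.
- *That the saline arm ceases to be a control for the primary objective.* Section 2.1 rests on AE incidence and on laboratory and clinical changes, none of them filtered by causality.
- *That the trial risks a false significant safety finding.* Fisher's exact test gives p = 0.093 for 4 of 12 against 0 of 12, and p = 0.037 for 5 of 12 against 0 of 12. With complete loss under saline, 5 or more EV reactions have probability 0.4%, 7.3% and 27.6% at q = 10%, 20% and 30%, against rejection probabilities of 0.3%, 1.2% and 1.7% when both arms are coded alike. The arithmetic is right, but 11.5 is descriptive and plans no such test.

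One could also say that the point is moot because the Safety Analysis Set, read literally, contains no saline subject. That is a separate defect. Repairing it would bring saline subjects in, but their events could still be coded unrelated at source.

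**Conclusion.** The point holds for one derived quantity. Followed literally, and with an assessor who knows the arm, 10.3 biases the between-arm adverse-reaction rate against EV by fq, up to the full common rate q. If the vesicles also cause reactions of their own, the reported excess mixes the two and they cannot be separated. The conclusion assumes that nebulization reactions occur in both arms, that at least some assessors take the term in its 7.2 sense, and that they know the allocation. The first is foreseen in 10.6 and the second is open on the text; the third is probable but inferred. The size depends on q and f, which the documents do not supply. The point warrants a correction to the wording; it does not undermine the all-cause safety comparison.

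**What to change.** - In 10.3, judge relationship to the assigned study treatment, defined as nebulized EV or nebulized saline and including the nebulization procedure, with the same categories and the same counting rule in both arms. Align the term with 7.2, 5.4 and 5.5.
- Where feasible, have one of the follow-up physicians already provided for in 5.5.2 assign causality from AE records stripped of arm, batch and randomization number. Removing the arm alone is not enough: 5.5.1 uses blocks of two, so knowing one subject's allocation reveals the paired one.
- Present the adverse-reaction rate as a descriptive supplement to the all-cause by-group summary that 11.5 already contains.

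The cost is a few lines of wording and some extra handling to mask the AE records. It needs no additional patients, visits or procedures.

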**2.1. Primary Objective**

To evaluate the safety of inhaled extracellular vesicle therapy in patients with pulmonary fibrotic lesions as identified by high-resolution computed tomography (HRCT).

1. to monitor vital signs, clinical symptoms and signs, and the incidence of adverse events on Days 1–8, Week 4, and Week 12 after enrollment.
2. to assess changes in laboratory and clinical parameters on Day 8 and Week 12, including complete blood count, urinalysis (plus pregnancy test), blood biochemistry, electrocardiogram (ECG), peripheral oxygen saturation (SpO₂), tumor markers, levels of IL-6 and IL-10, immune cell function in peripheral blood, and lymphocyte subsets.

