# 11. Statistical Analysis of Study Results

**11.1. Dataset Definitions**

- 1. Full Analysis Set (FAS)

All randomized subjects, regardless of whether they received aerosolized EV treatment are included. Analysis will be conducted according to the Intention-To-Treat (ITT) principle.

- 1. Per-Protocol Set (PPS)

Randomized subjects who received at least one dose of the assigned aerosolized EV treatment and had no major protocol deviations, as well as control subjects who did not receive EV aerosol treatment are included. Criteria for exclusion from the PPS will be defined prior to database lock and will be detailed in the statistical analysis plan.

- 1. Safety Analysis Set (SAS)

Randomized subjects who received at least one dose of aerosolized EVs are included. This set will be used for all safety evaluations. Subjects who were not randomized but received the study treatment will have their safety data listed separately and used only for overall safety evaluation of the study treatment.

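### Section 10.3 defines the adverse-reaction incidence inconsistently: the set of related categories contradicts its own list, events are divided by people, and the denominator is ambiguous

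*Protocol*

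**What the plan says.** Section 10.3 sets a five-point causality scale: "Causality categorized as: definitely related, probably related, possibly unrelated, unrelated, or indeterminate". It then says which grades count: "The first three categories (definitely, probably, and indeterminate) are considered related to the investigational product". These grades "will be used for calculating incidence rates of adverse reactions". The same sentence then gives the formula: "with the number of such events as numerator and the total number of participants as denominator for safety evaluation".

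Three other places bear on this rate. The primary objective in section 2.1 includes the aim "to monitor vital signs, clinical symptoms and signs, and the incidence of adverse events on Days 1–8, Week 4, and Week 12 after enrollment", with no restriction to related events. Section 11.5 says "The incidence of adverse events in each group will be summarized" and "Safety analyses will be based on the Safety Analysis Set and conducted by treatment group", but gives no counting unit. Section 11.1 defines the Safety Analysis Set thus: "Randomized subjects who received at least one dose of aerosolized EVs are included".

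**The concern.** Safety is the primary objective of this trial of 24 patients, so readers will look first at the proportion who had a reaction attributed to the product. Section 10.3 is the only place in the protocol that says how any adverse-event rate is calculated, and two analysts following it faithfully could report different figures from the same data. They could differ on which events enter the numerator, and on whether the denominator is one arm or both. Even where they agree, the figure called an incidence would not be the proportion of patients affected.

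The scale also lacks a possibly related grade. An investigator holding that view has to record probably related, possibly unrelated or indeterminate. Whether the event then counts depends partly on that forced choice and partly on which half of the contradictory sentence the analyst follows.

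**Working it through.** The protocol states no adverse-reaction rate, so there is no figure to reproduce. The check reads the rule literally and compares it with the sections around it. All event counts below are assumed for illustration; none comes from the protocol.

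**Inputs from the protocol.** 24 participants, 12 per arm (section 6). Two nebulizations a day for 7 days (section 7.2), so 2 × 7 = 14 exposures per patient, which makes repeat events in one patient plausible.

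**1. Which events count.** The listed order is (1) definitely related, (2) probably related, (3) possibly unrelated, (4) unrelated, (5) indeterminate.
- By position, the first three are items 1, 2 and 3.
- By name, the three in parentheses are items 1, 2 and 5.

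The two readings differ whenever the counts in items 3 and 5 differ. Assume one arm has 1 definite, 2 probable, 3 possibly unrelated, 4 unrelated and 2 indeterminate events, and apply the events-over-participants rule with 12 in the arm:
- By position: (1 + 2 + 3)/12 = 6/12 = 50%.
- By name: (1 + 2 + 2)/12 = 5/12 = 42%.

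**2. Counting unit.** Let *a* be the number of patients affected, *k* the related events per affected patient, and *N* the denominator. The section 10.3 rule gives *a* × *k*/*N*; the proportion of patients affected is *a*/*N*. They agree only when *k* = 1. With *a* = 3 patients in one arm:

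| Events per affected patient | Events | Events/12 | Events/24 | Patients affected/12 |
|---|---|---|---|---|
| 1 | 3 | 25% | 12.5% | 25% |
| 2 | 6 | 50% | 25% | 25% |
| 5 | 15 | 125% | 62.5% | 25% |

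With 12 in the arm, the ratio passes 100% as soon as there are more than 12 related events.

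**3. Denominator.** Three readings are open:
- Total number of participants, taken literally, is 24.
- Section 11.5 calls for analysis by treatment group, which points to 12 per arm.
- The Safety Analysis Set of section 11.1, taken literally, contains only patients who received EVs, so the placebo arm would have no denominator at all.

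For events arising in one arm, moving from 12 to 24 halves the figure: 6 events give 6/12 = 50% or 6/24 = 25%. That exact halving assumes no related events in the other arm.

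**The case against.** A reader might infer that the trial's primary safety rate is wrong. The protocol does not support that. Section 2.1 concerns all adverse events whatever their cause, together with vital signs, symptoms and laboratory changes. Section 10.3 governs only those judged related, and no single primary safety rate is named. Section 11.5 summarises adverse events, treatment-emergent events and serious events by group without invoking the section 10.3 formula, and no stopping rule or threshold uses it.

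A reader might also infer that the plan pools the two arms. That is not established either. Section 11.5 requires safety analysis by treatment group, so a per-arm denominator is a natural reading of the loose phrase in section 10.3. The fair charge is ambiguity. Figures with 24 in the denominator are therefore conditional. Related events could also be recorded under placebo, in which case pooling need not halve anything.

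Events per participant is, moreover, a legitimate measure when labelled as an event rate. And all adverse events are recorded regardless of relationship (sections 10.1 and 10.3) and listed in detail (section 11.5), so a patient-level incidence per arm can still be derived.

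These points stand, and they limit the severity. They do not remove the contradiction over which categories count. The last point also does not fully cover causality. The unit and the denominator can be corrected from the listing, but a judgement of possibly related that was forced into another grade can be recovered only by reassessment. The trial is single-blind (section 4.1), and section 5.5.2 says that staff are blinded to each other's assessments without expressly saying to allocation. Regrading, or choosing between the two related sets, after results are known would be open to bias.

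**Conclusion.** The point holds as a fault of definition in a supporting safety measure. Two defects are certain from the text: the related set contradicts its own list, and a ratio of events to people is called an incidence. The third, the denominator, is an ambiguity whose literal reading conflicts with section 11.5.

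The size depends on data not yet seen. Under the assumed counts above, the choice of related set moves the figure between 50% and 42%, and repeat events turn 25% of patients affected into 125%. Reading the denominator as 24 rather than 12 would halve a one-arm figure, provided there are no related events in the other arm. Severity is moderate: the reported rate changes, but the event data needed for a sound patient-level rate will be collected, with the reservation about forced causality grades.

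**What to change.** Before any unblinded review of safety data, amend section 10.3 as follows.

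1. Reconcile the category list and the named related set into one rule, applied identically in both arms. The sponsor should confirm which categories count as related and whether a possibly related grade was intended; the text does not settle either question.
2. Define adverse-reaction incidence as the number of participants with at least one related event, divided by the number dosed (EV or placebo) in the same arm.
3. Report the number of related events separately, labelled as event counts.
4. Align the denominator wording with section 11.5, and make sure that the safety set in section 11.1 gives the placebo arm a denominator.

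The cost is wording in section 10.3, with a matching line in section 11.1. If the grades change, the causality options on the case report form change too, and any events already graded need reassessment. No new visits or tests are required.
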